## Abstract

**Background:**

Medication adherence and lifestyle modification remain key in the management of hypertension. Leveraging mobile technologies to improve patient adherence has been found to be effective in chronic disease management. Given the high mobile penetration and the opportunities it provides for encouraging lifestyle modification, an app such as WhatsApp, which is a free-to-use and real-time messaging platform, could facilitate patient-clinician interactions. We present a protocol for a WhatsApp-led mobile health (mHealth) intervention to improve adherence to medication and healthy lifestyles among adults aged 40 to 59 years in Kerala, India.

**Objective:**

The study aims to assess the impact of the WhatsApp-led mHealth strategy on blood pressure measures and adherence to medication and lifestyle modification. The study also focuses on exploring participants’ views on feasibility, facilitators, and challenges, as well as their intention to use this WhatsApp-led mHealth strategy.

**Methods:**

The study will follow a multiphase mixed methods (sequential explanatory) design with an initial quantitative phase (quasi-experimental study design) followed by a qualitative phase (phenomenological approach). Multistage cluster sampling will be adopted. Using a survey checklist and blood pressure measurements, community-dwelling adults aged 40 to 59 years will be screened for hypertension. Approximately 120 participants with hypertension will be assigned each to the intervention and control arms. All the participants will be advised to follow routine hypertension care from health care providers. Additionally, participants in the intervention arm will receive regular health messages and reminders over WhatsApp. A baseline survey will be conducted at enrollment, and a follow-up survey will be conducted after 3 months at the end of the intervention. The qualitative phase will involve follow-up interviews. Participants will be selected through quota sampling from those with the lowest and highest adherence to medication and lifestyle modification after receiving the intervention. Statistical analysis for survey data and thematic analysis for qualitative data will be conducted.

**Results:**

The study received ethics approval (IHEC/CUK/2024/04) from the Institutional Human Ethics Committee of the Central University of Kerala. All 240 participants were recruited by July 2025. The study completed data collection in August 2025 and is expected to finish data analysis by April 2026. The study results are expected to be submitted for publication in July 2026.

**Conclusions:**

The study will be a potential strategy to address nonadherence to treatment and lifestyle regimens, which is a critical bottleneck to controlling hypertension and preventing complications. The study could be proof for a WhatsApp-led mHealth strategy that can be integrated into hypertension management at the community level, especially for improving hypertension awareness and reminders for behavior change.

## Introduction

Increased blood pressure levels are considered a prominent risk factor for cardiovascular diseases, which account for one-third of the deaths in India [1]. Uncontrolled hypertension is associated with nonadherence to medication and healthy lifestyle practices [2,3]. For the management of chronic conditions such as hypertension, India’s National Health Policy 2017 encourages the deployment of digital technologies to supplement routine health care. Digital technologies for hypertension management have been shown to promote treatment adherence and encourage lifestyle modification (ie, increased physical activity and better diet) [4-9].

Adults in the age group of 40 to 59 years are a crucial demographic for hypertension management. They have a greater risk of developing hypertension than their younger counterparts and better odds of controlling blood pressure compared to individuals older than 60 years. Major bottlenecks for hypertension management and control in this group lie in lifestyle modification and adherence to medication. Given the high mobile penetration, better digital literacy, and the opportunities for encouraging lifestyle modification that they provide, mobile-based interventions could be particularly effective among this population group for facilitating chronic disease management. WhatsApp, as a free-to-use and cost-effective app with better ease of use and user acceptance, has been increasingly used in organizational communication, monitoring, and delivery of services. As a real-time messaging platform, it has been shown to facilitate patient-clinician interactions [10,11]. Instant messaging through WhatsApp can facilitate mobile health (mHealth) services by acting as a medium for communicating reminders, health advice, and hypertension management guidelines [5,6,9,12,13].

A significant challenge of disease-specific mHealth apps is limited acceptance and ease of use among end users (patients). Given that hypertension management includes adherence to medicine and lifestyle changes, behavior change communication through WhatsApp-mediated reminders could function as cues to action and subsequently promote hypertension management. The effectiveness and feasibility of such an intervention are yet to be explored.

In this study, we aim to assess the impact of a WhatsApp-led mHealth strategy on blood pressure measures and adherence to medication and lifestyle modification among adults with hypertension aged between 40 and 59 years. The study also explores the participants’ intention to use the mHealth strategy and their views on the feasibility, facilitators, and challenges of using a WhatsApp-led mHealth strategy for adhering to medication and a healthy lifestyle for hypertension management. The conceptual framework adopted for the study (Figure 1 [14]) explains the facilitators and challenges of adopting the mHealth strategy for medication and lifestyle adherence using the Andersen-Newman behavioral model of health service use, unified theory of acceptance and use of technology, and health belief model [15-17].

**Figure 1. F1:**
[figure not shown]
Conceptual framework for the study. Clinically, hypertension control is achieved when systolic blood pressure is below 140 mm Hg and diastolic blood pressure is below 90 mm Hg as a result of lifestyle modification or medication [14]. mHealth: mobile health.

## Methods

### Study Design and Protocol

The study will adopt a multiphase mixed methods approach with a sequential explanatory design: an initial quantitative phase followed by a qualitative phase. The study protocol follows the Mixed Methods Reporting in Rehabilitation and Health Sciences guidelines, mHealth Evidence Reporting and Assessment checklist, and Transparent Reporting of Evaluations with Nonrandomized Designs statement [18-20].

### Study Setting and Population

Given the high prevalence and low control rates of hypertension in the Malabar region of Kerala, India, especially in Kannur [21,22], the study will be conducted among adults aged 40 to 59 years in the Kannur district, Kerala.

### Quantitative Phase of the Study

#### Study Design

The quantitative phase will use a quasi-experimental study design with an intervention group and a control group. This phase is designed to assess the effectiveness of the WhatsApp-led mHealth intervention on blood pressure estimates and medication and lifestyle adherence among individuals with hypertension.

#### Sample Size

A total study sample size of 240, with 120 each in the intervention and control arms, was estimated based on the estimates of diastolic blood pressure at baseline (mean 80.9, SD 10.9 mm Hg) and the postintervention time point (mean 75.4, SD 11.5 mm Hg) from a previous randomized controlled trial in Kerala [23]. *OpenEpi* was used for sample size calculation. The sample size was estimated at 80% power, a 95% CI, a 20% nonresponse rate, and a design effect of 1.5.

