#### Sampling

The study followed a multistage cluster sampling method. In the first stage, all taluks in the Kannur district were listed, and then 1 taluk (ie, Payyanur taluk) was selected. One rural (ie, Karivellur-Peralam gram panchayat) and one urban (ie, Payyanur municipality) administrative unit (cluster) from this taluk were then selected for the study (Figure 2). In stage 2, a door-to-door household survey will be conducted in these 2 rural and urban clusters. Household members aged 40 to 59 years will be screened for eligibility after consent is obtained. In the third stage, eligible participants (those with hypertension and access to WhatsApp) will be surveyed. After the baseline survey, the study’s recruitment will follow a nonrandomized approach (Figure 3) without matching or blinding as these are not applicable in this study setting. Upon recruitment and consent, the first participant will be allocated to the intervention group, and the next participant will be allocated to the control group. The participants will be recruited into the intervention and control groups sequentially in a 1:1 ratio. This process will be conducted iteratively until the sample size of 240 is reached (ie, 120 in the intervention group and 120 in the control group). At the cluster level, this amounts to 120 participants per cluster (urban and rural), with 60 of them in the intervention group and 60 in the control group.

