The follow-up survey time point of 3 months after the intervention was determined based on the review period (ie, 3 months) for lifestyle and blood pressure measurement changes as per the hypertension management protocol of the Department of Health Services, Government of Kerala [24]. This duration of 3 months is also based on the minimum period required for behavior changes or to develop new habits, including physical activity and dietary changes [12,44,45]. The long-term sustainability of behavior change and the durability of the mHealth intervention will be explored through the qualitative interviews. Even though the intervention ends after 3 months, the ability to keep the messages for an indefinite time, as well as the option to create a backup in WhatsApp, allows the participants to go through the messages again if needed after the intervention period.

WhatsApp is a ubiquitous platform that is not primarily meant for medical communication. However, given the real-time nature of WhatsApp-based intervention and health messaging specific to the individual participant, this study is expected to be effective in improving adherence to medication and healthy lifestyle and have better participant engagement with the mHealth intervention.

The individualized delivery method, with a person-to-person (researcher-to-participant) messaging system rather than a WhatsApp group or community, will help minimize contamination between the intervention and control groups. Additionally, all participants will be recruited from their homes and monitored regularly during the follow-up period until the end-line survey. In addition, during sample size estimation, the researcher accounted for the cluster effect to obtain an adequate sample size to prevent the reduction in the samples’ power due to contamination.

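### The 120 per arm at 80% power rests on a before-after change in diastolic pressure used as a between-arm difference, and on a design effect that does not fit the arm comparison; true power may be above or below 80%

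*Protocol article*

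**What the plan says.** The Sample Size section gives the total and its split: "A total study sample size of 240, with 120 each in the intervention and control arms". The effect size comes from two time points of an earlier trial in Kerala. The calculation is "based on the estimates of diastolic blood pressure at baseline (mean 80.9, SD 10.9 mm Hg) and the postintervention time point", the latter with a mean of 75.4 and an SD of 11.5 mm Hg. The section does not say which arm of that trial supplied these diastolic blood pressure (DBP) means, or whether they are pooled. The remaining inputs follow: "The sample size was estimated at 80% power, a 95% CI, a 20% nonresponse rate, and a design effect of 1.5".

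Other sections describe what is compared:

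- **Study Design (quantitative phase):** an intervention group is set against a control group.
- **Statistical Analysis:** effectiveness is assessed with generalized estimating equations (GEE) that include time, intervention and their interaction.
- **Sampling:** individuals are allocated alternately, 1:1. Each of the two areas (one urban, one rural) contributes 120 participants, "with 60 of them in the intervention group and 60 in the control group".
- **Standard Hypertension Care:** every participant, controls included, receives health education and advice on medication, monitoring and visits.

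Expected Findings, in the Discussion, returns to the sample size and says that "the researcher accounted for the cluster effect to obtain an adequate sample size to prevent the reduction in the" power of the sample, naming contamination as the cause of that reduction.

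**The concern.** A before-after change and a between-arm difference are different quantities. A change from baseline can contain movement that controls also show: time trend, regression to the mean in people who enter on a high screening reading, and the response to education given to everyone. The time-by-intervention interaction removes that shared part, and power for it depends on the net difference between arms. The article states no such difference.

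The design effect is a second mismatch. It allows for correlated observations when whole clusters are compared, or when a mean is estimated from a cluster sample. Here both arms sit in equal numbers inside both areas, so differences between areas largely cancel from the arm comparison. Contamination is a different problem again: it shrinks the true difference and leaves the variance alone.

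The risk is in interpretation. A small or null blood pressure result would be read against an 80% power claim that was not computed for the comparison being made, and a reader cannot tell which between-arm difference the trial could detect.

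**Working it through.** **Inputs.** Means 80.9 and 75.4, SDs 10.9 and 11.5, 80% power, 20% nonresponse and design effect 1.5 (Sample Size); two-sided 5% (Statistical Analysis). Difference = 80.9 − 75.4 = 5.5 mm Hg. Common SD = √[(10.9² + 11.5²)/2] = 11.20. All results use the normal approximation.

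**1. Reproducing 120.**
n per group = (10.9² + 11.5²)(1.96 + 0.8416)² / 5.5² = 65.1, so 66.
66 × 1.5 = 99; 99 × 1.2 = 118.8, so 119, against 120 stated. Dividing by 0.8 in place of multiplying by 1.2 gives 123 or 124, depending on rounding.

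The alternatives tried do not come near 120:

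| Variant | Per group |
|---|---|
| One-sided 5% | 94 to 98 |
| 90% power | 165 |
| Paired before-after, correlation 0.3 / 0.5 / 0.7 | 86 / 61 / 37 |

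So the two time points were entered as two independent groups.

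**2. Effect of the design effect.** Without it, the same inputs need 66 analysed, or 66/0.8 = 82.5, so 83 enrolled per arm. The factor of 1.5 therefore raised enrolment from about 83 to 120 per arm.

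**3. Power at the enrolled size for a true between-arm difference Δ.**
Power = Φ(Δ / [11.20 × √(2/n)] − 1.96). The value n = 96 takes the 20% as loss from analysis (120 × 0.8); n = 120 assumes none. Keeping the 1.5 with 96 gives an effective n of 96/1.5 = 64.

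| Δ (mm Hg) | n = 96, no design effect | n = 120, no design effect | n = 96, design effect 1.5 |
|---|---|---|---|
| 5.5 | 92.5% | 96.7% | 79.3% |
| 4.5 | 79.5% | 87.5% | 62.3% |
| 4.0 | 69.6% | 79.0% | 52.4% |
| 3.0 | 45.8% | 54.5% | 32.8% |
| 2.0 | 23.5% | 28.2% | 17.1% |

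The Δ values below 5.5 are illustrations; the article gives no between-arm figure.

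**4. Difference detectable at 80% power, by analysis.**
- *Follow-up means:* 2.80 × 11.20 × √(2/96) = 4.53 mm Hg; with 120 per arm, 4.05 mm Hg.
- *Time-by-arm interaction (difference in change):* SD of change = √(10.9² + 11.5² − 2r × 10.9 × 11.5). The pre-post correlation r is not given, so a range is assumed. With 96 per arm:

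| Assumed r | SD of change | Detectable difference (mm Hg) |
|---|---|---|
| 0.3 | 13.26 | 5.4 |
| 0.5 | 11.21 | 4.5 |
| 0.7 | 8.69 | 3.5 |

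- *Follow-up adjusted for baseline (analysis of covariance):* 4.53 × √(1 − r²); at r = 0.5, 4.53 × √0.75 = 3.92 mm Hg.

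**The case against.** The strongest reply is that the errors offset each other and that nothing in the data changes. The design effect raised enrolment by nearly half, so without it the trial has 80% power for about 4.5 mm Hg, which is smaller than the 5.5 planned for. Recruitment and data collection are complete, and the result will be read from its confidence interval. That stands, and it limits the seriousness of the point.

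A second reply is that an article condenses the full protocol, which may hold more detail. That excuses brevity. It does not excuse the basis that is stated: the two time points are named as the source of the sample size, and 120 follows from them without any further input.

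Several stronger readings are tempting, and the documents do not support them:

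- *A net 5.5 mm Hg requires no change at all in controls.* It requires only that the intervention arm fall 5.5 more than control. Regression to the mean and the common education act on both arms. Subtracting an assumed control-arm fall from 5.5 would also fix the intervention arm's total fall at the earlier trial's figure, which nothing in the article supports.
- *The 5.5 mm Hg came from a single arm.* The source arm is not stated. The point holds either way, since both means are time points.
- *Exactly 96 per arm will be analysed.* The article says nonresponse, reports all 240 recruited, and plans an intention-to-treat analysis with some imputation but also case deletion. Hence the columns for both 96 and 120.

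Some correlation within households is possible, but the article gives neither an intracluster correlation nor a household basis for the 1.5.

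**Conclusion.** The point holds as an error in the stated basis for sample size and power, and it should be fixed. The 80% is power for 5.5 mm Hg between two independent groups under a design effect of 1.5; the trial's own test is a difference in change between arms, within areas. A reader might infer that the trial is underpowered. The documents do not show that. With 96 analysed per arm, SD 11.2 and no design effect, the stated 80% is too low if the true between-arm difference exceeds about 4.5 mm Hg and too high if it is smaller; which of these applies is unknown.

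The statement that the cluster allowance protects power against contamination is wrong as written, whatever the effect size.

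These figures assume that the earlier trial's SDs apply here and that DBP is analysed as a continuous outcome. The Statistical Analysis section says that GEE results will be given as odds ratios, so the mm Hg figures describe a continuous DBP model only. The interaction figures also depend on the assumed correlation: at r = 0.5 the interaction gains nothing over follow-up means, and at r = 0.3 it does worse.

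**What to change.** No further enrolment is needed. The changes are:

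1. **Sample Size.** State that 5.5 mm Hg is a before-after change in an earlier trial, and name the arm it came from. Then give the between-arm DBP difference detectable at 80% power for the enrolled size, labelled by analysis: for follow-up means, 4.5 mm Hg with 96 per arm and 4.05 with 120; for the time-by-arm interaction with 96 per arm, about 5.4, 4.5 and 3.5 mm Hg at assumed correlations of 0.3, 0.5 and 0.7. Show power at 2, 3 and 4 mm Hg. Quote 3.9 mm Hg (r = 0.5) only if a baseline-adjusted analysis is adopted; it does not belong to the interaction test.
2. **Design effect.** Drop it from the arm comparison, or justify it with an intracluster correlation. Include the urban/rural unit as a fixed factor in the model.
3. **Expected Findings.** Correct the sentence on contamination: it dilutes the effect and is not covered by a design effect. Individual messaging can remain as the measure against it.

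The cost is a few sentences and one covariate, before the analysis is finished (expected April 2026). The sponsor gives up a single 80% figure for a range that depends on stated assumptions, and it is less favourable if the true difference is small.

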#### Sampling

The study followed a multistage cluster sampling method. In the first stage, all taluks in the Kannur district were listed, and then 1 taluk (ie, Payyanur taluk) was selected. One rural (ie, Karivellur-Peralam gram panchayat) and one urban (ie, Payyanur municipality) administrative unit (cluster) from this taluk were then selected for the study (Figure 2). In stage 2, a door-to-door household survey will be conducted in these 2 rural and urban clusters. Household members aged 40 to 59 years will be screened for eligibility after consent is obtained. In the third stage, eligible participants (those with hypertension and access to WhatsApp) will be surveyed. After the baseline survey, the study’s recruitment will follow a nonrandomized approach (Figure 3) without matching or blinding as these are not applicable in this study setting. Upon recruitment and consent, the first participant will be allocated to the intervention group, and the next participant will be allocated to the control group. The participants will be recruited into the intervention and control groups sequentially in a 1:1 ratio. This process will be conducted iteratively until the sample size of 240 is reached (ie, 120 in the intervention group and 120 in the control group). At the cluster level, this amounts to 120 participants per cluster (urban and rural), with 60 of them in the intervention group and 60 in the control group.

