#### Validity and Reliability of the Tools and Measurements

The content and face validity of the tools were improved through literature and peer reviews. All the adapted questionnaires used for the study will be tested for internal consistency using Cronbach α values. Physical measurements and blood pressure measurements will be taken by the principal investigator of the study, who is a trained medical graduate with a Bachelor of Ayurvedic Medicine and Surgery and a Master of Public Health and currently pursuing a PhD in Public Health. Standard equipment and specific cutoffs will be used as per standard protocols for blood pressure [30], waist circumference, and waist-to-hip ratio measurement [35]. The electronic blood pressure monitor will be checked for accuracy using a calibrated sphygmomanometer from the health center.

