## Discussion

### Expected Findings

The study will develop an mHealth strategy to improve medication and lifestyle adherence for hypertension management. WhatsApp was considered a suitable platform as it is cost-effective and user-friendly. Moreover, it does not need to be separately downloaded and subscribed to like other apps as most people already use it for regular messaging [10,11].

The study seeks to establish a proof of concept for a WhatsApp-led mHealth strategy that can be integrated into hypertension management at the community level. This strategy could function as a means for timely reminders and encourage individuals to change their behavior, improving medication adherence and lifestyle modifications [40]. Similar approaches could be adopted for individuals with other chronic noncommunicable diseases. Moreover, health care professionals, especially frontline health workers, can contact, provide information to, and receive updates from patients through WhatsApp as instant messaging platforms such as this one can facilitate mHealth services by acting as a medium for communicating health advice and hypertension management guidelines [5,6,9,12,13].

Selecting only 1 taluk from the Kannur district is a major limitation. However, considering that there are similarities in the sociodemographic and economic conditions, linguistic homogeneity (the predominant language is Malayalam), and commonalities in the political and administrative factors, the findings could be generalized to the context of Kerala as a whole. The study adopted a quasi-experimental study design with an intervention group and a control group because the main aspects of a randomized controlled trial, such as randomization, matching, and blinding, cannot be applied in this context. Unlike other trials, this study uses an mHealth intervention, which acts as a platform for sending hypertension awareness messages and reminders for a healthy lifestyle and medication adherence in addition to the routine hypertension care available in health centers. There could be limitations in establishing causal conclusions about the observed effects. However, the qualitative interviews with the participants who received the intervention could help obtain a deeper understanding of their experiences with and adoption of the intervention to adhere to a healthy lifestyle and medication.

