The findings from the study will contribute to improving the planning and implementation of mHealth services for managing chronic diseases such as hypertension in India and other similar settings. Tailoring health messages specifically to the individuals could be challenging. However, prestructuring the messages will be helpful for easy dissemination. The researcher will recruit 4 batches of approximately 30 participants each into the control and intervention groups and then start sharing the messages individually with the participants in the intervention group. The entire intervention will be completed in these 4 batches. This is only for the convenience of the participants and the researcher to reduce the gap between the baseline survey and the first day of the intervention. The end-to-end encryption option of WhatsApp helps protect each individual’s chat data, and saving the participants’ contact information using code names will help protect their privacy.

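### Unconcealed strict alternation leaves the arm contrast open to selection bias, and the statement that randomization could not be applied is given no support

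*Protocol article*

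**What the plan says.** The Sampling section of the quantitative phase sets the rule: "the first participant will be allocated to the intervention group, and the next participant will be allocated to the control group". It adds: "The participants will be recruited into the intervention and control groups sequentially in a 1:1 ratio". This repeats until 240 people are enrolled, with 60 per arm in each of the rural and urban clusters. Allocation comes after the baseline survey: "Upon recruitment and consent, the first participant will be allocated". The section also says that "recruitment will follow a nonrandomized approach (Figure 3) without matching or blinding as these are not applicable in this study setting".

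The Discussion (Expected Findings) explains the quasi-experimental design by saying that "randomization, matching, and blinding, cannot be applied in this context". It adds one general caution about causal conclusions. The same section describes delivery as a "person-to-person (researcher-to-participant) messaging system rather than a WhatsApp group or community" and says of recruitment: "The researcher will recruit 4 batches of approximately 30 participants each into the control and intervention groups". Under Validity and Reliability of the Tools and Measurements, "Physical measurements and blood pressure measurements will be taken by the principal investigator of the study".

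The Statistical Analysis section plans chi-square tests, unadjusted odds ratios, t tests or rank tests, and a generalized estimating equations (GEE) model. The terms named for that model are time, intervention, their interaction and sociodemographic factors. The Results section reports that all 240 participants were recruited by July 2025, that data collection ended in August 2025, and that analysis should finish by April 2026.

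**The concern.** Under alternation with a known starting arm, anyone who knows the last assignment knows the next one. The baseline survey comes first, so the recruiter can know a person's blood pressure, treatment status and apparent interest while also knowing which arm is due. The order of approach, the effort made to persuade, or a borderline eligibility decision could then depend on the arm. Differences produced in this way would be read as intervention effects on blood pressure, adherence and lifestyle. Most of those outcomes are self-reported and plausibly linked to motivation.

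The second part concerns the stated reason. A reader of the Discussion would conclude that predictable allocation was unavoidable. The article gives no ground for that, and it mentions neither concealment, nor predictability, nor selection bias.

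**Working it through.** **Sample size, to fix the yardstick.** The inputs are in the Sample Size section: diastolic pressure 80.9 (SD 10.9) at baseline and 75.4 (SD 11.5) after intervention, 80% power, 95% confidence, 20% nonresponse, design effect 1.5.

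- Planning difference: 80.9 − 75.4 = 5.5 mm Hg.
- n per arm = (10.9² + 11.5²)(1.96 + 0.8416)² / 5.5² = 65.14, rounded up to 66.
- Design effect: 66 × 1.5 = 99.
- Nonresponse: 99 × 1.2 = 118.8, so 119 per arm and 238 in total, which agrees with the stated 240. Dividing by 0.8 instead gives 124 per arm, or 248.

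The allocation point does not depend on this number. The 5.5 mm Hg serves only as a scale.

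**Predictability.** Under the stated rule, 240 of 240 assignments are known in advance. For comparison, take permuted blocks of 4, 6 and 8 in random order within each cluster. A recruiter who tracks past assignments and always guesses the under-represented arm is right about 68% of the time (simulation), or about 71% with fixed blocks of 4. Random blocks would have reduced predictability, but would not have abolished it for an unblinded recruiter.

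**Stated reason against the design.** Assignment is individual, 1:1 and after consent, and messages go to one person at a time. Wherever the next person can be given the alternate arm, the next person can also be given the next entry on a concealed list, with the same total. Lack of blinding does not prevent this. In the Sampling section, the words on inapplicability grammatically cover matching and blinding. Only the Discussion extends them to randomization, and it gives no reason.

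**Illustrative size.** The documents give no steering rate, so 5% to 20% of consecutive pairs is an assumption. Diastolic pressure is taken as normal with SD 10.9 and independent between consecutive people.

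- Expected absolute difference within a pair: 2 × 10.9 / √π = 21.8 / 1.772 = 12.3 mm Hg.
- Baseline gap if the lower-pressure person is steered to intervention: 12.3 × 0.05 = 0.6; 12.3 × 0.10 = 1.2; 12.3 × 0.20 = 2.5 mm Hg.
- As a share of 5.5 mm Hg: 11%, 22% and 45%.

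**What the planned contrast leaves.** A time-by-intervention term compares changes. Let g be the baseline gap (intervention lower) and ρ the baseline to follow-up correlation. With equal SDs and no true effect, the follow-up gap is ρg, so the contrast in change is off by (1 − ρ)g. With ρ assumed at 0.5 to 0.7:

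- smallest: 0.3 × 0.6 ≈ 0.2 mm Hg;
- largest: 0.5 × 2.5 ≈ 1.2 mm Hg.

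In this scenario the error runs against the intervention; steering the other way reverses it. The calculation treats diastolic pressure as continuous. The article says GEE results will be given as odds ratios and does not say how blood pressure enters the model. Conditioning the follow-up value on the baseline value would remove selection on measured baseline pressure under a linear model. Neither approach removes selection on motivation or engagement.

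**The case against.** The design is openly declared. The article calls itself quasi-experimental, nonrandomized and unblinded, follows the reporting statement for nonrandomized designs, is registered as nonrandomized, and carries a causal caveat. Nobody is led to believe that allocation was random. This stands, and it limits the point to an unsupported justification, an unnamed bias mechanism and an analysis that could do more against it.

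Several stronger readings are tempting but are not supported:

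- **That selection bias occurred.** Nothing in the article shows steering. It also does not say outright that the researcher who recruits is the principal investigator who measures, although the point needs only an unblinded recruiter.
- **That the infeasibility statement is false.** An article may condense a reason given elsewhere. What can be said is that no obstacle is named and that the described procedure suggests none.
- **That up to 45% of the planning difference could be spurious.** That figure is a baseline gap under an assumed steering rate, much of which the change contrast removes. In a simple follow-up comparison, a persisting 2 mm Hg shift would raise a 5% false-positive rate to about 28% at 120 per arm. However, blood pressure is not in the article's list of outcomes for that test.
- **That alternation split households between arms.** Household members are screened, but the text does not say whether more than one was enrolled. Individual randomization would also split about half of any such pairs.

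It is also fair to say that covariates are often left to an analysis plan, and that the list of GEE terms is open-ended. Still, the covariates that matter for this allocation method are not among those named, and naming them now is easy.

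**Conclusion.** The concern holds in limited form. Every assignment was predictable to an unblinded recruiter, so the between-arm contrast is exposed to selection bias, and the claim that randomization could not be applied is unsupported by the design described. The amount of bias is unknown.

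As an illustration only, steering 5% to 20% of pairs on diastolic pressure gives a baseline gap of about 0.6 to 2.5 mm Hg, with about 0.2 to 1.2 mm Hg left in a change contrast if the correlation is 0.5 to 0.7. Both the steering rate and the correlation are assumptions. Selection on unmeasured traits cannot be quantified from the article and would survive the planned model.

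**What to change.** Recruitment is complete, so the allocation rule must be reported as it was carried out. Rewriting it as randomization would misdescribe the study.

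1. **Wording.** In Expected Findings, justify or withdraw the statement that randomization could not be applied. In Sampling, describe allocation as unconcealed alternation. Name selection bias from predictable allocation as a limitation.
2. **Analysis.** In Statistical Analysis, make the main between-arm comparison adjust for the baseline value of the outcome, rural or urban cluster, medication status (where the outcome is not confined to treated participants) and screen-detected versus known hypertension. It should not rest on unadjusted odds ratios and sociodemographic factors alone. Fix this before the arms are compared, and date the change.
3. **Reporting.** Where logs allow, tabulate persons approached, eligible and refusing by the arm that was next in sequence. If more than one member of any household was enrolled, use standard errors that allow for it; otherwise this is not needed.

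The cost is small: some wording and slightly more analysis. Cluster, baseline outcomes, diagnosis and medication status are already collected. The refusal table depends on a sequence log that the article does not describe, so it may not be possible. Adjustment cannot remove selection on unmeasured factors, and the report should say so.
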